#### Secondary outcomes

##### Coping capacity

Personal coping resources are evaluated using the Sense of Coherence scale (SOC) [48,49]. The SOC short version scale consists of 13 items on a 7-point Likert scale. The SOC scale evaluates perceived comprehensibility (5 items), manageability (4 items) and meaningfulness (4 items). A higher score represents a stronger sense of coherence [50]. The reliability and validity of the SOC scale has been proven in many studies and different languages with a Cronbach’s α range of 0.74 to 0.93 [51-53].

##### Symptom experience

Symptoms (frequency, severity and distress) are measured using the Memorial Symptom Assessment Scale (MSAS), a multidimensional questionnaire consisting of 32 symptoms [54]. The MSAS generates the Total Symptom Burden Scale (TMSAS) and the Global Symptom Distress Index (GDI). The MSAS has been proven to be a reliable and valid multidimensional measure of symptom experience in cancer populations [54,55].

##### Health-related quality of life

Breast cancer specific HRQoL is evaluated using the 10 item visual analogue scale of the International Breast Cancer Study Group Quality of Life Core Questionnaire (IBCSG QoL). The questionnaire includes global indicators for physical well-being, mood, coping, social support and subjective health estimation, and indicators of symptoms covering possible specific disease and treatment-related effects. Higher scores indicate a higher level of symptoms/problems. The reliability and validity of the questionnaire has been established in several studies [56,57].

##### Health status

The SF-36 measures eight domains of health including physical functioning, role limitations due to physical health, bodily pain, general health perceptions, vitality, social functioning, role limitations due to emotional problems, and mental health [58]. The SF-36 yields a score for each of these eight domains, a total score for physical and mental health, and a global health utility index. Maximum score is 100 points. Higher scores indicate better health status. The reliability measurements of the SF-36 are consistently good [58-61].

##### Personal growth

Posttraumatic Growth Inventory (PTGI) is a measure of positive life changes after traumatic or life-altering events [62]. The PTGI consist of 21 items, rated on a 6-point Likert scale, divided into five dimensions: Relating to others (7 items), New possibilities (5 items), Personal strength (4 items), Spiritual change (2 items), and Appreciation of life (3 items). The PTGI yields a score for each of these subscales, and a total score. The PTGI has shown good reliability in previous research of breast cancer survivors, with Cronbach’s alpha for the PGI total score was 0.96 [63].

##### Mindfulness

Five Facets of Mindfulness Questionnaire (FFMQ short form). FFMQ developed by Baer and colleagues [64]. The FFMQ short form consists of 29 items, and yield five factors that appear to represent elements of mindfulness as it is currently conceptualized: Observing, Describing, Acting with awareness, Non-judging of inner experience and Non-reactivity to inner experience.

##### Blood sampling

NK cell function will be measured using a newly developed assay called flow cytometric assay of natural killer cell immune response in activated whole blood (FANKIA; 1). Briefly the cell line K562 is mixed with whole blood and the mix is centrifuged and incubated in 37°C for 2 hours. After staining with an antibody that recognizes K562, the number of remaining K562 cells is determined using flow cytometry and the lytic activity of the NK cells is calculated. Flow cytometry will be performed using a standard multicolour procedure to detect the main lymphocyte populations in human blood. Staining for regulatory T cells will also be performed. Cytokine analyses of IL-6 and IL-8 in serum will be performed using the automatic enzyme immunoassay system Immulite 1000 according to the standard procedure from the manufacturer.

##### Health check-ups

Research nurses will conduct health check-ups including blood pressure and heart rate, at baseline and follow-ups. A protocol for baseline socio- demographics and medical characteristics, and follow-up protocols for current medical conditions, including disease progression, will be used to report health status.

##### Analyses of utility and health economics and usability of MBSR

The utility of MBSR in clinical settings, and health economic impact and costs will be described in relation to sick leave, health care patterns, drug costs and mortality.

### Sample size calculation

To detect significant differences between three groups (MBSR Intervention I and II, and non-MBSR): 50 participants per group (150 participants in total) are needed in order to achieve a statistical power of 80%. The power calculation was based on alpha of 0.05 and expected mean effect size difference between the groups (difference in change between baseline and 3 months follow-up) being at least 1 unit at HAD-scale.

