### Statistical analyses

Descriptive statistics will be used to summarize socio-demographic and clinical characteristics. Pearson’s correlation coefficient will be calculated to determine the strength of relationships between selected variables. Univariate and multivariate analyses of variance for repeated measures (ANOVA/MANOVA) will be used to compare between groups. For comparison of skewed variables, a non-parametric test will be used. Regression analyses will be used to identify predictors. In multivariable stepwise procedures only variables that provide statistically significant contributions will be included in the analyses (p < 0.05).

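### Pre-specified adjustment for baseline HAD would make the 3-month comparison more precise than the change-score contrast to which the plan points

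*Protocol article*

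**What the plan says.** The Sample size calculation section of the protocol article states that "50 participants per group (150 participants in total) are needed" for 80% power. It adds that "The power calculation was based on alpha of 0.05" and on an "expected mean effect size difference between the groups (difference in change between baseline and 3 months follow-up") "being at least 1 unit at HAD-scale". No standard deviation and no baseline-to-follow-up correlation are given.

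The Statistical analyses section then says: "Univariate and multivariate analyses of variance for repeated measures (ANOVA/MANOVA) will be used to compare between groups". It adds: "For comparison of skewed variables, a non-parametric test will be used". No baseline term is named for the group comparison. Regression appears only as a means of finding predictors, and stepwise models there keep a variable only if p < 0.05.

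According to the Participants section, questionnaires are completed at the baseline appointment and random assignment comes last. Baseline HAD is therefore a pre-randomisation measurement. The same section describes randomisation in blocks of 9, 12 and 15 and mentions no stratification by HAD.

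**The concern.** A change score subtracts the whole baseline value, which fixes the baseline coefficient at 1. HAD scores at two visits are imperfectly correlated, so the slope of follow-up on baseline will usually be below 1. Two consequences follow.

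- **Precision.** Subtracting too much of the baseline adds noise, so 50 women per group yield less information than they could.
- **Chance imbalance.** An arm that starts higher by chance will tend to fall further through regression to the mean, and the change score credits part of that fall to treatment. Nothing described in the design balances baseline HAD across arms of 50.

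Both affect the primary outcome, at the contrast on which the trial is powered, and the remedy uses data that the trial already collects.

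**Working it through.** **Inputs.** From the document: alpha 0.05 (two-sided assumed, as sidedness is not stated), power 80%, 50 per group, difference 1 HAD unit. Assumed: r between 0.2 and 0.9, and equal SD s at baseline and 3 months.

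**1. The plan's own figure.** It cannot be reproduced without an SD, but the SD it implies can be solved for. For a pairwise comparison, n = 2·SD²·(1.960 + 0.842)²/1², so SD = √[50/(2 × 2.802²)] ≈ 1.785 for the change score. A t-test version gives 1.767. A three-group F test gives 1.84 or 1.59, depending on the pattern of means (1, 0, 0 or 1, 0.5, 0). The implied SD of change is thus about 1.8 on the pairwise reading.

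**2. Equivalence.** With two time points, the group-by-time interaction in a repeated-measures ANOVA is the between-group test on (3 months − baseline).

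**3. Variances.**
- Change score: Var = 2s²(1−r)
- Baseline-adjusted (ANCOVA): Var = s²(1−r²)
- Ratio = (1+r)/2, so the cut is (1−r)/2.

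The direction of the result does not need equal SDs. With SDs s0 and s1, the change-score variance minus the adjusted variance is s0² + s1² − 2r·s0·s1 − s1²(1−r²) = (s0 − r·s1)². This is never negative, and it is zero only when the slope r·s1/s0 equals 1.

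**4. Size, taking the 80% at face value (SD of change 1.785).** Adjusted power = Φ(2.802/√ratio − 1.960). For r = 0.5: 2.802/√0.75 = 3.235, less 1.960 = 1.275, which gives 89.9%.

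| r | variance cut | 50 per group acts like | power at 50 per group |
|---|---|---|---|
| 0.2 | 40% | 83 | 95.1% |
| 0.4 | 30% | 71 | 91.8% |
| 0.5 | 25% | 67 | 89.9% |
| 0.6 | 20% | 62 | 87.9% |
| 0.7 | 15% | 59 | 86.0% |
| 0.8 | 10% | 56 | 84.0% |
| 0.9 | 5% | 53 | 82.0% |

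(Third column: 50/ratio.) A simulation of 20,000 two-arm trials with 50 per arm gave cuts of 28.8% at r = 0.4 and 14.5% at r = 0.7. These are slightly below the formula because the slope has to be estimated.

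**5. Size if the SD of change is larger (assumed).** With change scores, power at 50 per group is 52%, 39% and 30% for SDs of 2.5, 3.0 and 3.5 (normal approximation). At SD 3.0, the noncentral t gives 37.9% for change scores, 45.4% with adjustment at r = 0.6 and 47.8% at r = 0.5.

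**6. Chance imbalance.** Averaged over simulated trials, both estimates had a mean error of about 0. Given an observed baseline difference, the change-score estimate moved by −0.60 per unit at r = 0.4 and −0.30 at r = 0.7, matching −(1−r). The adjusted estimate moved by about 0. For scale, at r = 0.5 the implied s is 1.785, so the standard error of a baseline difference between two arms is 1.785 × √(2/50) = 0.357. An imbalance of one standard error then shifts the change-score result by 0.5 × 0.357 ≈ 0.18 unit, against a target of 1 unit.

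**The case against.** The strongest reply is that nothing here is an error. A randomised comparison of change is valid, the article never says that the analysis is unadjusted, and the choice of covariates often belongs in an analysis plan that is not shown. Moreover, the 3-month contrast comes from the sample size text, while follow-up includes 6 and 12 months and then yearly visits to 5 years. With more than two visits the interaction is no longer just the change-score test.

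Much of this stands. The absence of adjustment is inferred, and a fuller plan could add the covariate. But the article is not silent: it names a change contrast for power and a method for comparing groups, and reserves regression for predictors. Later visits do not alter the comparison at 3 months, which is the contrast that was powered.

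Three stronger readings are tempting and are not supported.
- **That the planned comparison is biased.** It is not, over randomisation. The error arises only conditionally, given an observed baseline imbalance.
- **That adjustment is known to save 15-30% of the variance.** Those figures require r of 0.7 to 0.4, and the document gives no correlation.
- **That the trial falls short of 80% power.** The document gives no SD. At the SD it implies, power is 80% by construction, and the 38% rests on an assumed SD of 3.0. The missing SD is a separate matter.

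**Conclusion.** The point holds as an improvement in efficiency and robustness, not as the correction of an invalid analysis. Under a linear model, adjusting for baseline HAD is never less precise in large samples than the change score, and it is more precise unless the slope of follow-up on baseline is exactly 1. With equal SDs the variance falls by 40% to 5% over r = 0.2 to 0.9. On the plan's implied SD of change, power rises from 80% to about 92% at r = 0.4 or 86% at r = 0.7. If the SD of change were 3.0, it would rise only from about 38% to 45-48% at r = 0.6 to 0.5, so adjustment would not by itself restore 80%. The direction of the gain is firm; its size depends on r and the SD, neither of which is in the document.

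**What to change.** In the Statistical analyses section, state that the primary estimate is the between-arm difference in each HAD subscale at 3 months, from a linear model with the baseline score of that subscale as a pre-specified covariate. Say explicitly that this covariate stays in the model regardless of its p-value and is outside the stepwise p < 0.05 rule. Report unadjusted change descriptively.

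Apply the same baseline adjustment to other outcomes measured at baseline. Because the plan makes separate provision for skewed variables, specify a transformation or a rank-based version with baseline adjustment for those likely to be skewed, such as IL-6 and IL-8.

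The cost is a few sentences and one degree of freedom per model, with no extra data or participants. The change should be fixed before outcome data are examined.

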### Statistical analyses

Descriptive statistics will be used to summarize socio-demographic and clinical characteristics. Pearson’s correlation coefficient will be calculated to determine the strength of relationships between selected variables. Univariate and multivariate analyses of variance for repeated measures (ANOVA/MANOVA) will be used to compare between groups. For comparison of skewed variables, a non-parametric test will be used. Regression analyses will be used to identify predictors. In multivariable stepwise procedures only variables that provide statistically significant contributions will be included in the analyses (p < 0.05).

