## Methods

### Design

Patients diagnosed with early stage breast cancer will be consecutively recruited from two surgical centers, to participate in this three-armed randomized controlled complementary intervention study. The study design is presented in Figure 1.

Written consent will be obtained before enrolment. Confidentiality will be assured, and participants will be advised that they are free to withdraw from the study at any time, and respect will be given to the participant’s condition. The study is registered in ClinicalTrials.gov: NCT01591915.

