### Data collection

Socio-demographic data will be collected through chart review and interviews. Data characteristics are age, marital status, living situation, employment status, children, occupation and educational level. Clinical characteristics investigated are type of treatment, tumor characteristics, and co-morbidity. Patient self-reported response (questionnaires) and immune response (blood samples) will be collected, and health checks conducted, at baseline (before start of intervention), after the intervention for MBSR Intervention groups I and II, follow-up will be conducted one months after the intervention, and at similar time points of 3 months (non-MBSR), 6 months, 12 months, and thereafter yearly up to 5 years. Health checks including current health status and treatment, and blood samples will be performed by research nurses. Patient outcome will be collected by following the questionnaires, health check-ups and bio-markers.

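### Repeated-measures ANOVA/MANOVA conventionally keeps only women complete on every visit entered, and it is not tied to the 3-month HAD change on which the trial was sized

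*Protocol article*

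**What the plan says.** Statistical analyses gives the between-group method in one sentence: "Univariate and multivariate analyses of variance for repeated measures (ANOVA/MANOVA) will be used to compare between groups". It adds a fallback: "For comparison of skewed variables, a non-parametric test will be used". It does not say which visits enter the model, which term is tested (group, time or group-by-time), or whether the fallback applies to HAD.

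Sample size calculation is specific about time. The 50 women per group (150 in all) rest on a "difference in change between baseline and 3 months follow-up) being at least 1 unit at HAD-scale", with alpha 0.05 and 80% power, to detect differences between three groups. It gives no standard deviation and no allowance for loss.

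Data collection schedules a baseline, a visit at about 3 months, and then "6 months, 12 months, and thereafter yearly up to 5 years". That makes seven follow-ups: 3, 6, 12, 24, 36, 48 and 60 months. Under Design, participants are told that "they are free to withdraw from the study at any time". The primary outcome, anxiety and depression on HAD, carries no time point.

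**The concern.** Classical repeated-measures ANOVA and MANOVA work on a complete vector of outcomes per woman, so each visit added to the model removes the women who missed it. A woman whose 3-month HAD was observed would drop out because she missed, say, the 36-month visit. The arms differ sharply in contact (weekly group sessions, home programme, standard care only) and the trial is unblinded. Loss that is related to distress and differs by arm is therefore plausible, and a completers' comparison can then be biased.

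A group-by-time test over all visits also asks whether the arms' profiles differ anywhere over five years. The sample size concerns one change, from baseline to 3 months. The primary conclusion could then rest on a test whose power was never assessed.

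The fallback adds a smaller problem: read literally, the observed skewness decides which test the primary outcome receives.

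**Working it through.** **1. The plan's own figure.** The 50 per group cannot be reproduced, because no SD of change is given. It can be solved backwards. For a two-sided comparison of two arms:

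SD = 1 / [(1.960 + 0.842) × √(2/50)] = 1 / (2.802 × 0.2) = 1.78.

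Other readings of the same sentence give 2.01 (one-sided), 1.55 (Bonferroni over three pairs) and 1.59 to 1.84 (three-group F-test with a range of means of 1). The two-sided pairwise reading is used below.

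**2. Women left, by visits entered.** The documents give no rate of missed visits. Assume a chance d of missing each visit, independent across visits. The complete fraction over v follow-ups is r = (1 − d)^v. At the implied SD, power for the 1-unit 3-month difference with 50r women per arm is Φ(2.802·√r − 1.960).

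| Follow-ups entered | d | r | Women per arm | Power |
|---|---|---|---|---|
| 3 months only (v = 1) | 5% | 0.95 | 47.5 | 78% |
| | 10% | 0.90 | 45 | 76% |
| 3, 6, 12 months (v = 3) | 5% | 0.857 | 42.9 | 74% |
| | 10% | 0.729 | 36.5 | 67% |
| All seven (v = 7) | 5% | 0.698 | 34.9 | 65% |
| | 10% | 0.478 | 23.9 | 49% |

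Example, last row: 2.802 × √0.478 − 1.960 = −0.02, and Φ(−0.02) = 0.49. Noncentral t calculations, with an implied SD of 1.77, agree to within about one percentage point.

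For v = 3 and v = 7 the table measures only the cost of losing women. It applies the 3-month comparison to women complete on every visit entered, and is not the power of an all-visit test.

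**3. Which hypothesis is tested.** With only baseline and 3 months in the model, the sole within-woman contrast is the difference Y(3) − Y(0). The group-by-time F-test is then identical to a one-way ANOVA of the 3-month change, which is the quantity sized. With more visits it is not.

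**4. Power of the all-visit test with no missing data.** Simulation: 2,000 runs per scenario, 50 per arm, eight assessments, compound symmetry with correlation 0.5, SD of change 1.785, Intervention I versus control differing by 1 unit at 3 months.

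| Effect pattern | Intervention II | MANOVA interaction | Univariate interaction | Pairwise 3-month test |
|---|---|---|---|---|
| 3 months only | half a unit | 60% | 63% | 80% |
| Fading | half the effect | 72% | 76% | 80% |
| Sustained | half a unit | 59% | 62% | 78% |
| 3 months only | full unit | 77% | 79% | 78% |
| Fading | full effect | 85% | 88% | 80% |
| Sustained | full unit | 77% | 80% | 78% |

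Monte Carlo error is about one point. A separate run with SD 2.5 and correlation 0.75 (SD of change 2.5 × √0.5 = 1.77) and Intervention II at half gave 64% for the univariate interaction under both the sustained and the 3-month-only pattern. The group main effect varies more: with Intervention II at half it has 7% power for a 3-month-only effect and 85% for a sustained one.

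**The case against.** The strongest reply is that the article never says visits to 5 years enter one model. Read together with the sample size section, the analysis could use baseline and 3 months only. It would then test the sized quantity and lose only women without a 3-month score, leaving power near 76% to 78% under the assumed rates. This stands. A reader might infer that any woman with one missed visit in five years will be excluded, but the documents do not say so. Listwise deletion is how the method conventionally behaves, not a written rule, and its handling may be set out in an analysis plan that is not shown.

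Three further objections also stand. The sample size is itself framed as differences between three groups, so an omnibus group test does not contradict it; the mismatch concerns the time points and the tested term. The all-visit interaction test does not always lose power. And completers' analysis is not biased by every departure from loss completely at random: loss that depends on arm alone does no such harm.

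On the fallback, it would be too strong to say that a rank test rules out baseline adjustment or an estimate in HAD units. It can be run on change scores, and a Hodges-Lehmann shift is in HAD units. No HAD distribution is given, so heavy skewness is a possibility, not a fact.

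What the reply does not remove is that the article has already chosen a method, that the method conventionally needs complete vectors, and that nothing in its wording points to the 3-month change.

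**Conclusion.** The point holds in conditional form. The named method is poorly suited to a schedule of seven follow-ups with free withdrawal, and it is not tied to the 3-month change. If only 3 months enters, little is lost. If later visits enter, observed 3-month scores are discarded: under the assumed rates completers fall to 86% or 73% (to 12 months) or 70% or 48% (all seven), and bias becomes possible.

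It is tempting to conclude that the trial has 65% or 49% power instead of 80%. The documents do not support that. Those figures combine a 3-month comparison with a completeness requirement over all visits, and they rest on assumed missed-visit rates, independence across visits and a back-solved SD. They are the far end of a range that starts at 78% or 76%. Nor can one say that the all-visit interaction test is weaker in general: the simulated range is about 60% to 88%, depending on the effect pattern.

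This should be corrected because a better-matched method is available at little cost.

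**What to change.** Analyse HAD with a likelihood-based mixed model for repeated measures in all randomised women, using every observed score: arm, visit, arm-by-visit, baseline HAD and an unstructured covariance. Make the between-group comparison at 3 months the primary test, state whether it is the three-group test or named pairs, and treat later visits as secondary. Keep this model as primary whatever the observed skewness, with robust or bootstrap standard errors as a check and rank tests as sensitivity analysis.

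The cost is a change of analysis wording and slightly more analysis work in standard software; no new data are needed. The model relies on loss being missing at random given the observed scores, which cannot be verified, and a woman with no follow-up score still adds no outcome information.

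### The stepwise rule (keep only p < 0.05) gives invalid p-values, under-covering intervals and inflated coefficients in the predictor regressions; the between-group comparison is not affected

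*Protocol article*

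**What the plan says.** The Statistical analyses section of the protocol article gives two separate jobs to two separate methods.

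- Comparing the arms: "Univariate and multivariate analyses of variance for repeated measures (ANOVA/MANOVA) will be used to compare between groups", with a non-parametric test where variables are skewed.
- Looking for predictors: "Regression analyses will be used to identify predictors". The next sentence fixes how terms are chosen: "In multivariable stepwise procedures only variables that provide statistically significant contributions will be included in the analyses (p < 0.05".

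No candidate list is given for the regressions, no term is named as always kept, and the results are not described as exploratory. Data collection lists seven socio-demographic items ("age, marital status, living situation, employment status, children, occupation and educational level") and three clinical domains (treatment, tumour, co-morbidity). These are data to be collected; the article does not call them regression candidates.

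Sample size calculation gives 50 women per group, 150 in all, for 80% power at alpha 0.05 to detect at least 1 HAD unit ("difference in change between baseline and 3 months follow-up"). It states no SD.

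**The concern.** The rule uses the same data twice: first to decide which variables stay, then to supply the p-values, intervals and coefficients reported for those that stayed. A variable is seen only if its estimate was large enough to pass the threshold. Standard regression output ignores that filter, so the evidence for each retained predictor looks stronger, and its effect larger, than it is.

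This is a method and threshold written into the text, so an analysis plan that follows the article would inherit it. At stake is the credibility of any predictors the trial reports. There is also a conditional risk: if arm or baseline score were entered in these models, the sentence as worded would let either be removed for lack of significance.

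**Working it through.** **Inputs from the article.** Keep terms only at p < 0.05; 150 women, 50 per group; 80% power, alpha 0.05 (taken as two-sided), 1 HAD unit.

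**Assumptions.** 10 to 20 independent candidates; complete data; forward selection with backward removal at 0.05; three true standardised effects of 0.15 for step 1; SDs of 2.5 to 3.5 for step 2.

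**The plan's own figure.** With no SD stated, 50 per group can only be back-solved. For two groups, SD = 1 / [(1.960 + 0.842) × √(2/50)] = 1 / (2.802 × 0.2) = 1.78. A three-group F test gives 1.59 to 1.84, depending on the pattern of means. The sample size is neither confirmed nor disputed here; the SD is used in step 2.

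**1. Inflation and coverage of retained terms.**

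- For standardised variables, SE ≈ 1/√150 = 0.082, so an estimate must exceed about 1.96 × 0.082 = 0.16 to stay. A true effect of 0.15 lies below that cut-off, so it can be retained only when overestimated.
- Expected value once retained: 0.15 + 0.082 × φ(0.12)/[1 − Φ(0.12)] = 0.15 + 0.082 × 0.396/0.451 ≈ 0.22.
- Simulation (2,000 data sets, 10 candidates, three true effects of 0.15): mean retained true coefficient 0.23; each true effect kept in 42% of models; 95% intervals for all retained terms covered 72%. A separate run gave 0.23 and 74%.
- A full prespecified model on the same data gave 0.15 and 95%.
- Source of the shortfall: intervals for retained true terms covered 93%, but a retained null term has an interval that excludes zero by construction. Per model, about 3 × 0.42 = 1.27 true and 7 × 0.05 = 0.35 null terms are kept, so coverage ≈ 1.27 × 0.93 / (1.27 + 0.35) = 0.73.

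**2. Arm, only if it is entered as a candidate.** True effect δ = 1, two arms of 50. SE = SD × √(2/50), z = 1/SE. P(dropped) ≈ Φ(1.96 − z). Mean if kept ≈ 1 + SE × φ(1.96 − z)/P(kept). The simulation adds 10 noise candidates (1,500 data sets per row).

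| SD | SE | Dropped, formula | Dropped, simulated | Mean if kept, formula | Mean if kept, simulated |
|---|---|---|---|---|---|
| 1.785 (implied) | 0.357 | 20% | 22% | 1.12 | 1.12 |
| 2.5 (assumed) | 0.50 | 48% | 52% | 1.39 | 1.39 |
| 3.0 (assumed) | 0.60 | 62% | 61% | 1.60 | 1.61 |
| 3.5 (assumed) | 0.70 | 70% | 71% | 1.81 | 1.81 |

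**3. Baseline score, only if it is entered.** With 150 women, a predictor correlated 0.3 with the outcome reaches p < 0.05 with probability Φ(√147 × 0.3095 − 1.96) = Φ(1.79) ≈ 96%, where 0.3095 = atanh(0.3). At 0.4 it is about 99.9%. Loss of baseline score would be uncommon unless it is weakly related to the outcome.

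**4. False predictors when no candidate matters** (150 women, 1,000 data sets per row).

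| Candidates | 1 − 0.95^k | Stepwise, at least one kept | Full model, at least one p < 0.05 |
|---|---|---|---|
| 10 | 40% | 40% | 38% |
| 15 | 54% | 54% | 52% |
| 20 | 64% | 63% | 58% |

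The last two columns are close. This rate is ordinary multiplicity and does not isolate a harm of stepwise selection.

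**The case against.** The strongest reply is scope. The article gives the arm comparison to ANOVA/MANOVA and regression a different purpose, and predictor identification is not among its primary or secondary outcomes. That stands, and it excludes several stronger readings that a reader might infer:

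- *That the rule endangers the efficacy result.* It governs the predictor regressions only.
- *That arm and baseline HAD are subject to it.* The text never names them as candidates; it only fails to protect them if they are. The larger drop-out rates also rest on SDs that the article does not give.
- *That the 40 to 64% false-predictor rates measure the harm of stepwise selection.* A full model with the same candidates gives nearly the same rates.
- *That the plan lists ten or more candidates.* It lists data to be collected.
- *That most reported predictors would fail to replicate.* Simulations without true predictors cannot show that, and the article does not say how many true predictors to expect.

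It can also be said that a model with arm and baseline score is an efficacy model and does not find predictors. That does not hold against a prespecified list in which the predictors of interest sit beside arm and baseline score. Covariate sets that differ by outcome are no fault in themselves when each outcome has its own predictors.

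None of this defends reporting p-values, intervals and coefficients as if no selection had taken place.

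**Conclusion.** Wrong as written, limited to the secondary predictor analyses. That selection at p < 0.05 invalidates the subsequent p-values, costs interval coverage and inflates retained coefficients follows from the rule itself. The size depends on assumptions: with 150 women, 10 independent candidates and three true effects of 0.15, the inflation is about half (0.23 against 0.15) and coverage for retained terms is about 72 to 74% instead of 95%. Stronger true effects would be inflated less.

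The risk to arm is conditional on arm being entered: about 20% of models would drop a true 1-unit effect at the SD implied by the plan's own power statement, and about 48 to 70% at assumed SDs of 2.5 to 3.5. The between-group comparison by ANOVA/MANOVA is not affected.

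**What to change.** Replace the stepwise sentence with the following:

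- For each outcome, a short predictor list chosen in advance, with arm and baseline score included and every term kept whatever its p-value. If screening is wanted, use penalised regression with bootstrap validation.
- Effect modifiers tested by interaction with arm.
- Predictor analyses labelled exploratory.

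Keeping all terms restores valid intervals and unbiased coefficients but does not lower the false-predictor rate. That needs a shorter list or a multiplicity-aware method: with independent null candidates, going from 10 to 5 lowers the chance of at least one false predictor per model from 40% to 1 − 0.95^5 = 23%.

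Cost: one sentence of text, fewer candidate predictors examined, and slightly more analysis work. No new data are needed.
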